### Procedure

All procedures will be carried out in line with the ethical standards laid out in the Declaration of Helsinki [32]. All procedures were approved by the Research Ethics Committee of the University of Thessaly, ref approval no. 39 (date of approval: 19/11/2020), the Ethics Committee of the Department of Physical Education & Sport Science, ref approval no. 1701 (date of approval: 09/12/2020) and the ethical review board of Northwest and Central Switzerland, ref approval no. AO_2020-00036 (date of approval: 26/11/2020). Prior to data assessment, all participants will sign written informed consent. On the consent form, participants will be asked if they agree to use of their data should they choose to withdraw from the trial. Participants will also be asked for permission for the research team to share relevant data with people from the universities taking part in the research or from regulatory authorities, where relevant. They will also be informed that the trial involves collecting blood specimen (10 drops) from every individual at each measurement occasion. Allocation to groups will be done randomly by a computer-generated code after the baseline assessment has taken place. In order to reduce random differences between the two groups, we will use the “OxMaR” software (Oxford Minimization and Randomization), taking into account the following stratification variables: gender, age, time fleeing and PTSD symptom severity. All data assessments will be made by trained research staff. At the post- and follow-up data assessment, assessors will be blinded with regard to group allocation. Since many participants will have limited English skills, all questionnaires will be provided in English, Arabic, Farsi, French and Greek, and a translator will be present during the data assessment. Main languages spoken in the camp are Arabic, Farsi, Koyrmatzi, Sorani, Somali and French.

Inclusion criteria are (a) written informed consent, (b) aged 16–59 years, (c) living in the selected refugee camp, (d) not having any contra-indications for moderate-intensity physical activity (based on the Physical Activity Readiness Questionnaire) [33], (e) being able to exercise at least two times per week for 60 min at moderate intensity and (f) being able to read English, Arabic, Farsi, French or Greek. In case of contra-indications, consultation with a medical doctor will be held. At the baseline, we will assess information about further concomitant care and interventions (e.g. use of antidepressants), in order to account for these factors as potential confounders/moderators.

### Recruitment and screening

All camp residents will receive detailed written and oral information about the planned intervention programme. During this process, we will screen as many camp residents as possible to obtain reliable information about the socio-demographic background of the camp residents. For this purpose, we will use a short questionnaire to collect information about residents’ age, nationality, religious background, educational background, time fleeing (in months), time in camp (in weeks), physical activity level during the past week and PTSD symptoms (using the 5-item Primary Care PTSD Screen for DSM-5 [34].

### Intervention

Exercise and sport activities will be offered five times per week (60 min/session) for 10 weeks. Separate programmes will be offered for men and women. Moreover, cultural particularities of the target population will be considered during programme development. In order to increase ownership, refugee camp residents will be involved in the development of the intervention programme. To this end, we will carry out short informal interviews and organize focus group discussions in order to develop appropriate programmes for both male and female participants. Participants are asked to participate in at least two sessions per week (but encouraged to do more). Participants can choose between a range of activities. Based on the experience from the pilot study [23] where 95% of the participants were satisfied or very satisfied, activities for males could include weight and endurance training, football, volleyball or other activities depending on the needs and preferences of the participants. The programme for female participants will also consider their needs and preferences. Due to possible language barriers or inter-cultural difficulties due to multi-ethnic background of refugees, it is important that the activities are tailor made, in particular, simple, acceptable, pleasant and easy to understand and apply to meet individual, gender, age, ethnic/cultural-specific needs and preferences in the real-life (pragmatic) setting of a refugee camp with limited exercise/sport facilities. Tailor-made interventions are highlighted by international physical activity guidelines for people with mental health problems [35] and proved to provide mental health benefits in both pragmatic (real-life) and clinical settings [36].

### Manipulation check

Participation in the exercise and sport programme will be systematically recorded during the intervention period via attendance lists. This will allow us to consider participation rate as a potential covariate. Furthermore, physical activity levels will be assessed via accelerometer devices during the baseline data assessment and during the intervention period (each time across a 7-day period). This will inform us whether the exercise and sport intervention was able to significantly increase the participants’ physical activity level. Moreover, each participant will wear a heart rate monitor during at least two training sessions to collect some information whether the average intensity of the exercise and sport intervention is in the targeted range (moderate intensity). According to the American College of Sports Medicine, activities of 64–75% of age-predicted maximum heart rate are considered “moderate” [37]. We will also regularly employ the widely used 6-20 Ratings of Perceived Exertion Scale [38] to regularly control participants’ perceived exertion [37]. This is important to ensure exercise safety and facilitate more comfortable experiences during exercise, given that common negative affective states in our sample such as stress, anxiety and depression are often associated with disturbed or more strenuous perceptions of exercise intensities [36, 39].

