**Fig. 2 Fig2:**
[figure not shown]
SPIRIT figure, providing an overview of timepoints, interventions and assessments of the planned pragmatic randomized controlled trial. *Notes.* *Wait-list control group only

This trial will be a pragmatic trial, carried out in a hosting site for refugees. The pragmatic design ensures increased external validity by replicating routine practice conditions including “real-life” settings and minimum exclusion criteria [27]. Also, a pragmatic design suggests that when therapist or participant blinding is not possible, such as in exercise or psychotherapy trials, it cannot be seen as a severe flaw because routine practice is also not blinded [28]. In particular, trials with blinded interventions cannot be considered fully pragmatic [29]. Moreover, collateral therapeutic interventions derived from treatment as usual conditions are not necessarily a bias factor in the context of pragmatic trials. Integrating a collateral intervention of this sort in a broader “complex” intervention represents what is typically seen in routine practice within a contemporary stepped collaborative care model. Accordingly, our findings from a pragmatic trial will be representative of routine practice and, thus, of increased external validity.

After an initial screening, participants will be assessed three times, at baseline (before the intervention), immediately post-intervention (after 3 months) and at follow-up (after 6 months). After the first 6-month follow-up, participants of the IG will have the choice whether they want to continue participation in the exercise/sport programme, whereas participants of the WLCG will start the 3-month intervention phase. The intervention duration is based on NICE guidelines that recommend 10–14 weeks for physical activity in adult depression treatment [30]. A further data assessment will be carried out with the WLCG to examine whether similar changes will occur as in the IG, after the WLCG has received the intervention programme. Interviews will be carried out during all intervention phases in order to continuously improve the quality of the exercise/sport programme.

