### Participants

Participants will be recruited from the “Koutsochero” refugee camp in the municipality of Larissa. Approximately 1500 residents live in this camp. In March 2020, 916 residents were aged from 16 to 59 years (62% men, 38% women). The population is diverse in terms of socio-demographic background. Most of the residents are from Syria (36%), Afghanistan (34%) and Iraq (14%), whereas the remaining 16% are from the Middle East or from the sub-Saharan region.

To estimate the minimal sample size, a power analysis was carried out using G*Power 3.1. Based on the pilot study of Knappe et al. [23], a weak-to-moderate effect can be expected on our primary outcome (PTSD symptoms; *f* = 0.19). However, in the pilot study, only males and a short-term intervention (8 weeks) were considered, and no longer-term follow-ups were carried out. Therefore, we do not know whether similarly strong effects would be found in women and whether similarly strong effects can be observed after a longer follow-up period. As a consequence, we have decided to use a slightly more conservative effect size estimate (*f* = 0.15). The mean difference in the primary outcome variable (immediately post) will be used as primary endpoint. With an α-error probability of 5%, a power of 0.8, three measurement timepoints (*r* = 0.5 between repeated measures) and four groups (one male and female IG and WLCG), a total number of 108 participants is needed. With an expected dropout rate of 25%, a total of 136 participants will be recruited (68 men, 68 women), with half of them being randomly assigned to the IG or WLCG. The expected dropout rate is based on our pilot study (16%) [23] and a meta-analysis in patients with major depression (15% in a more controlled/clinical setting) [31].

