#### Effects of the intervention

Multilevel modelling will be used to evaluate the effects of the intervention. The longitudinal analyses will be performed with linear mixed models (random effects). The within-person parameters (intercepts and slopes of outcome variables) at Level 1 will be conceptualized as dependent variables in Level 2 (between-person). Treatment conditions (as well as potential covariates) will be integrated as Level 2 predictor(s) to detect and explain between-person change over time [107]. In case of potential violation of prerequisites (e.g. non-normality of data) mixed logistic regression models will be applied.

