#### Dropout analyses and missing data handling

Before testing our main hypothesis, we will test whether those participants who completed all data assessments and those who dropped out after the first or the second data assessment differ with regard to their socio-demographic background or in one of the assessed study variables. In case of systematic differences, one can assume missing not at random (NMAR) and main analyses will be replicated using intent to treat techniques (e.g. last observation carried forward) to estimate the influence of dropout on the results. In any other case, missing data will be treated as random (MAR) and the multilevel modelling will be adapted whether by integrating obvious missing patterns (like dropout) as additional Level 2 predictor and/or by imputing missing data (FIML) for missing data without identifiable patterns [108].

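### The protocol leaves open adjusting the between-arm effect for attendance, a post-randomisation variable that is zero in every wait-list participant

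*Protocol article*

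**What the plan says.** All references are to the protocol article.

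- **Timing of randomisation (Procedure):** "Allocation to groups will be done randomly by a computer-generated code after the baseline assessment has taken place".
- **Timing of attendance (Manipulation check):** "Participation in the exercise and sport programme will be systematically recorded during the intervention period via attendance lists". The next sentence gives one purpose: "This will allow us to consider participation rate as a potential covariate".
- **Where covariates go (Effects of the intervention):** "Treatment conditions (as well as potential covariates) will be integrated as Level 2 predictor(s) to detect and explain between-person change over time".
- **When controls get the programme (Study design):** the intervention group may continue after the 6-month follow-up, "whereas participants of the WLCG will start the 3-month intervention phase". Wait-list attendance is therefore zero by design at both the post and the 6-month assessments.
- **Primary endpoint (Participants):** "The mean difference in the primary outcome variable (immediately post) will be used as primary endpoint".
- **Dropout (Dropout analyses and missing data handling):** where data are treated as missing at random, the multilevel model may be adapted by "integrating obvious missing patterns (like dropout) as additional Level 2 predictor", by full-information maximum likelihood, or by both.

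No section confines attendance to an analysis within the intervention group, or to a secondary or exploratory one.

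**The concern.** A covariate in a randomised comparison should not be a consequence of allocation. Attendance is one, and it is also the route by which an exercise programme would most naturally act. Since it does not vary among controls, adjusting for it compares the control group with a hypothetical intervention participant who never attended. That is a different question from the mean difference named as primary endpoint.

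An effective programme could then be reported as ineffective. If people who attend more differ in motivation or health, the comparison could also be biased by that selection. Because the choice is left open, the main estimate could depend on a decision taken after attendance is known.

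Dropout raises a milder version of the same issue. It also occurs after randomisation, and a bare dropout term turns the arm effect into one conditional on staying or leaving.

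**Working it through.** **1. The plan's own figure.** The Participants section gives f = 0.15, four groups, three timepoints, r = 0.5, α = 5% and power 0.8. For a repeated-measures within-between interaction, λ = f²·N·m/(1 − r), df1 = (k − 1)(m − 1) and df2 = (N − k)(m − 1). The smallest N is 105, which rounds up to 108 for four equal groups. There λ = 0.0225 × 108 × 3 / 0.5 = 14.58, df1 = 6, df2 = 208 and power is 0.817. The stated 108 is reproduced. It is used below as the number analysed, and this point does not change it.

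**2. What the arm coefficient becomes.** Let A be the share of sessions attended, with A = 0 for all controls. The slope b of outcome on A can then be learned only from the intervention group. With Δ the baseline-adjusted arm difference and Ā the mean attendance in the intervention group:

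adjusted arm coefficient = Δ − b·Ā

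This equals Δ only when b·Ā = 0.

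**3. Precision.** With 1:1 allocation and attendance mean μ and SD σ in the intervention group, R² of attendance on arm = μ²/(μ² + 2σ²), VIF = 1/(1 − R²), and the standard error is multiplied by about √VIF. The documents give no attendance figures, so two assumed settings are shown:

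- μ = 0.50, σ = 0.20: R² = 0.25/0.33 = 0.758, VIF = 4.1, √VIF = 2.0
- μ = 0.60, σ = 0.25: R² = 0.36/0.485 = 0.742, VIF = 3.9, √VIF = 2.0

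**4. Simulation.** The model is ANCOVA of the post score on arm and baseline (r = 0.5), with N = 108 and 4,000 replicates. Assumed attendance is mean 0.50, SD 0.20. The assumed total effect, where there is one, is −0.5 SD (negative is benefit). Cells show estimate (SE) and rejection rate.

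| Mechanism | b | Δ − b·Ā | Without attendance | With attendance |
|---|---|---|---|---|
| Benefit proportional to attendance | −1.0 | −0.5 + 0.5 = 0 | −0.50 (0.17), 0.84 | 0.005 (0.35), 0.05 |
| Constant benefit | 0 | −0.5 | −0.50 (0.17), 0.84 | −0.49 (0.35), 0.30 |
| No effect; motivation drives attendance and outcome | −0.4/0.2 = −2.0 | 0 + 1.0 = +1.0 | 0.00 (0.18), 0.04 | +1.01 (0.37), 0.78 |
| Proportional benefit plus the motivation link | −3.0 | −0.5 + 1.5 = +1.0 | −0.50 (0.19), 0.72 | +1.01 (0.37), 0.79 |

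The formula in step 2 predicts each simulated estimate. With neither an effect nor a motivation link, rejection stays at 0.05 with or without attendance.

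A second simulation used 51 per arm (136 × 0.75 = 102), attendance mean 60%, SD 25%, and proportional benefit, in 3,000 trials. The size of the estimate went from 0.50 (SE 0.17, power 80%) to 0.00 (SE 0.36, rejection 5%).

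**5. Link to the planned model.** The simulations use one post-baseline score, not the full mixed model. The same algebra applies when attendance predicts the person-level slope alongside arm. The protocol's statement that Level 2 predictors explain change over time points to that use.

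The dropout term was not simulated.

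**The case against.** **The wording is permissive.** Attendance is something to consider as a potential covariate, and it is mentioned under a manipulation check. A reader might infer that the primary analysis will be adjusted for attendance. The documents do not say so, and the primary endpoint is defined without it. This stands: the fault is an option left open.

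**The link between sections is an inference.** The effects section follows one that looks for potential covariates among baseline differences, so its covariates could all be baseline variables. That reading is possible. But the manipulation-check section uses the same term for a non-baseline variable, and nothing excludes that variable from the effect model. This is also why the point is more than detail left to an analysis plan: the article itself nominates an unsuitable covariate.

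**Legitimate uses exist.** Attendance is a reasonable exploratory dose variable within the intervention group, or in the later assessment after the wait-list group has had the programme. True, but the text does not limit it to those uses.

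**The effect need not vanish.** A reader might infer that the adjustment always removes the treatment effect. It does so only if benefit is proportional to attendance; a constant benefit is estimated without bias, though with twice the standard error. Nor is collinearity the main problem, since a VIF of about 4 is moderate. The main problem is the change in what is estimated.

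**Dropout patterns can be modelled validly.** A pattern-mixture model may enter them at Level 2, and the protocol's brief phrase does not rule that out. A reader might infer that any dropout term is wrong, which goes too far.

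**Physical activity during the trial.** The point does not extend to accelerometer data. The protocol uses them to check whether activity rose and does not propose them as a covariate.

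**Conclusion.** The point holds as an open option that should be closed. If participation rate enters the between-arm model, the arm coefficient no longer estimates the mean difference named as primary endpoint. That follows from zero attendance among controls and does not depend on any assumed figure.

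The size does depend on assumptions: attendance of mean 50–60% and SD 20–25%, an effect of 0.5 SD, and the mechanism. The outcome ranges from no bias with a doubled standard error (power 0.84 to 0.30), through a lost effect (power 0.80–0.84 to 0.05), to a reversed sign. With no true effect, a motivation link of the assumed strength gives false rejection of 0.78.

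Dropout is a secondary, unquantified point. In the missing-at-random branch, a likelihood-based mixed model needs no dropout term. A bare one would make the arm effect conditional on a post-randomisation event.

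**What to change.** - State that only baseline variables may be covariates in the between-arm effect model, for example the minimisation factors (gender, age, time fleeing, PTSD symptom severity) and baseline IES-R.
- Limit attendance to description, a labelled secondary complier-average analysis with allocation as instrument, or an exploratory dose-response analysis within the intervention group. The complier analysis should state its assumption that allocation acts on outcome only through attendance as defined.
- Keep the likelihood-based (FIML) mixed model without a dropout term as the main analysis. If dropout pattern is entered at Level 2, do so only as a sensitivity analysis, with arm-by-pattern terms averaged over patterns and a stated assumption for participants with no post-baseline score.

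The cost is a few sentences and slightly more analysis work. The attendance lists are already planned, so no new data are needed, and the sample size does not change.

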### Quantitative data collection and measures

Types of data to be collected include the following: quantitative data on socio-demographic background, PTSD symptoms, perceived stress, depressive symptoms, anxiety, sleep complaints, health-related quality of life, pain, cardiorespiratory fitness, upper-body muscular strength, physical activity, cognitive function and cardiovascular risk markers. With the exception of socio-demographic background, all variables will be assessed three times at baseline, post and follow-up.

#### Self-reported data

PTSD symptoms (primary outcome) will be assessed with the 22-item Impact of Event Scale-Revised (IES-R) [40]. The instrument is internationally accepted, not culturally specific, and is available in English [40], Arabic [41], Farsi [42], French [43] and Greek [44]. The IES-R items refer to DSM-V and ICD-10 criteria of PTSD. The IES-R has been used previously in refugee populations [45]. The IES-R provides a cut-off for a possible PTSD diagnosis [46]. In our pilot study [23], the IES-R had good internal consistency.

Perceived stress during the past month will be assessed with the 10-item Perceived Stress Scale (PSS) [47]. Participants will be asked how often they find their lives to be overwhelming, uncontrollable and unpredictable. The PSS is available in English [47], Arabic [48], Farsi [49], French [50] and Greek [51], and has been used in refugee populations [52].

Depressive symptoms will be assessed with the 9-item Patient Health Questionnaire (PHQ-9) [53]. Items of this instrument refer to DSM-V criteria for major depression. The PHQ-9 has been previously employed with refugee populations [54]. The instrument exists in English [53], Arabic [55], Farsi [56], French [57] and Greek [58].

Anxiety symptoms will be assessed with the 7-item General Anxiety Disorder (GAD-7) scale [59]. The GAD-7 exists in Arabic [55], Farsi [60], French [61] and Greek [62], and has been used previously with refugees [63].

Insomnia symptoms will be assessed with the Insomnia Severity Index (ISI) [64], a brief screening measure of insomnia and an outcome measure in treatment research, which takes into consideration the criteria for insomnia of the DSM-V [65]. Arabic [66], Farsi [67], French [64] and Greek [68] versions of the ISI exist, and the instrument has been used previously with refugees [69].

Health-related quality of life will be assessed with the five-item World Health Organization Index (WHO-5) [70], which is specifically designed for psychiatric populations [71]. The instrument exists in English [70], Arabic [72], Farsi [73], French [74] and Greek (see https://www.psykiatri-regionh.dk/who-5/who-5-questionnaires/Pages/default.aspx), and has been used with refugees previously [75].

Pain over the last week in several body regions (head, back, chest, stomach, upper and lower body extremities) will be measured with the Visual Analogue Scale for Pain (VAS) [76]. Evidence of the validity of the VAS has been reported previously [77], and the VAS has been used in refugee populations [78].

Self-perceived fitness will be assessed with a 1-item fitness measure [79]. Previous studies showed that self-perceived fitness is moderately associated with objective fitness measures [80] and more closely associated with subjective health perceptions than self-reported physical activity [81].

As part of the screening, participants will be asked to provide information about their socio-demographic background in order to assess potential confounders. In addition, participants will be asked to report doctor diagnosed diseases before the flight. During the intervention period, we will assess information about injuries that prevent participation in the exercise and sport, medication intake and the occurrence of critical life-events.

